# Protocol for a single-blind randomized clinical trial to test the efficacy of bilateral transcranial magnetic stimulation on upper extremity motor function in patients recovering from stroke

**DOI:** 10.1186/s13063-023-07584-7

**Published:** 2023-09-22

**Keywords:** Stroke, rTMS, Combined, Plasticity, Cortical excitability, Serum factor

## Abstract

**Background:**

No consensus currently exists regarding the optimal protocol for repetitive transcranial magnetic stimulation (rTMS) treatment of upper-extremity motor dysfunction after stroke. Studies have shown that combined low- and high-frequency stimulation (LF-HF-rTMS) of the bilateral cerebral hemispheres is more effective than sham stimulation or stimulation of one cerebral hemisphere alone in treating motor dysfunction in the subacute stage of stroke. The efficacy of this protocol in the convalescence phase of stroke has rarely been reported, and its mechanism of action has not been clarified. In this study, we designed a prospective, single-blind, randomized controlled trial to investigate the efficacy and safety of different stimulation regimens for the treatment of upper extremity motor disorders in patients with convalescent stage stroke and aimed to explore the underlying mechanisms based on biomarkers such as brain-derived neurotrophic factor (BDNF).

**Methods:**

Seventy-six subjects will be randomly divided into combined, low-frequency, high-frequency, and control groups based on the proportion of 1:1:1:1, with 19 cases in each group. All groups will have conventional rehabilitation, on top of which the combined group will receive 1 Hz rTMS in the unaffected hemisphere and 10 Hz rTMS in the affected hemisphere. The low-frequency group will be administered 1 Hz rTMS in the unaffected hemisphere and sham stimulation in the contralateral hemisphere. The high-frequency group will be administered 10 Hz rTMS in the affected hemisphere and contralateral sham stimulation. The control group will receive bilateral sham stimulation. Assessments will be performed at baseline, after 2 weeks of treatment, and at post-treatment follow-up at week 6. The primary outcomes are FMA-UE (Fugl-Meyer assessment-upper extremity), latency, and serum BDNF levels. The secondary outcomes are the National Institute of Health Stroke Scale (NIHSS), Brunnstrom staging (BS), modified Ashworth scale (MAS), Modified Barthel Index (MBI), central motor conduction time (CMCT), precursor proteins of mature BDNF (proBDNF), and matrix metalloproteinase-9 (MMP-9) levels. Adverse events, such as headaches and seizures, will be recorded throughout the study.

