### Sample size

We have calculated the sample size using the PASS 15 software. A literature search was conducted using FMA-UE as the primary indicator [8], specified as a two-sided test with *α* = 0.05 with a degree of certainty (test efficacy1-β) of = 0.8, and a total sample size of *N* = 60 cases was calculated. Considering a 20% dropout rate and the average distribution of each group, the total sample size was 76, with 19 individuals included in each group.

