### Data analysis

Data analysis will be performed by the SPSS 26.0 statistical software, and statistical analysis of efficacy will be based on intention-to-treat analysis (ITT) principles.We will check whether the data is normally distributed using the Shapiro Wilk normality test. Nonparametric analysis such as chi-square test will be applied for the count data, and it will be expressed as rate or composition ratio. Nonnormal data will be tested using the Kruskal–Wallis test.Paired *t*-tests will be used for pre- and post-treatment comparisons of groups, one-way ANOVA for inter-group comparisons, and Bonferroni correction for post hoc comparisons between groups.Two-factor repeated measures ANOVA will be employed to investigate the impact of within-group factors (time points) and between-patient factors (subgroups) on outcomes and to analyze main and interaction effects.Pearson correlation analysis will be performed to investigate the correlation between cortical excitability (latency and CMCT) and motor function (FMA), the relationship between serum factors (BDNF, proBDNF, and MMP-9) and motor function, and the correlation between cortical excitability and serum factors.

A *P* value of < 0.05 will be regarded as statistically significant.

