## Conclusion

Comprehensive assessment of clinical symptoms and functional scales for stroke patients combined with biological markers can be used to accurately assess the functional prognosis of stroke patients [42]. In this study, FMA-UE, latency, and serum BDNF levels will be used as the main indicators, as well as subjective and objective indicators such as NIHSS, BS, MAS, MBI, CMCT, pro-BDNF, and MMP-9, which will be used to comprehensively evaluate the efficacy of LF-HF-rTMS in enhancing upper limb movement. Based on the changes in nerve electrophysiology and serum factors in patients, we will explore the possible molecular mechanisms of rTMS promoting motor recovery of the upper extremities after stroke. This study is expected to offer new proof for potent protocols and biomarkers for rTMS to augment upper limb motility levels during stroke recovery.

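### Three unranked primary outcomes are each tested at P < 0.05 with no rule across them; if any one counts as success, familywise error is about 12–14% for correlations of 0 to 0.6

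*Protocol article*

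**What the plan says.** Three outcomes carry primary status. The abstract says "The primary outcomes are FMA-UE (Fugl-Meyer assessment-upper extremity), latency, and serum BDNF levels", the Primary outcomes section describes the same three, and the Conclusion repeats that "FMA-UE, latency, and serum BDNF levels will be used as the main indicators" in assessing efficacy. None is ranked above the others.

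The Data analysis section gives "one-way ANOVA for inter-group comparisons" and "Bonferroni correction for post hoc comparisons between groups", and also lists paired t-tests and a two-factor repeated measures ANOVA. It closes with a single criterion for all tests: a P "value of < 0.05 will be regarded as statistically significant".

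The Sample size section works from one outcome: "A literature search was conducted using FMA-UE as the primary indicator". It uses the full two-sided 0.05 and 80% power, obtains 60 patients, and raises this to 76 (19 per group) for 20% dropout.

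**The concern.** The one multiplicity correction in the text covers pairs of arms within an outcome. It does not cover the choice among three primary outcomes, each of which gets its own test at the full 0.05.

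The title and the stated aim concern upper-extremity motor function. As printed, nothing prevents a significant latency or serum BDNF result, with no FMA-UE benefit, from being reported as a positive primary finding. The 5% error rate that a reader would attach to the efficacy claim would then not apply.

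A second, separate gap is that the sample size says nothing about power for latency or BDNF, although both have the same status as FMA-UE.

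**Working it through.** **Inputs from the article**
- Three primary outcomes (Abstract, Primary outcomes, Conclusion).
- Threshold 0.05 for every test; one-way ANOVA across four groups (Data analysis).
- FMA-UE only, two-sided alpha 0.05, power 0.80, N = 60, 20% dropout, final N = 76 (Sample size).

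**Assumptions, not in the article**
- The correlation between the outcomes, so a range is shown.
- The decision rule, so both readings are worked through.
- The effect size behind N = 60, so it is solved backwards.

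**1. The plan's own figure.** 60 / (1 − 0.20) = 75, rounded up to a multiple of four = 76. Per group, 15 / 0.8 = 18.75, so 19. The 76 is reproduced. The 60 cannot be re-derived, because no effect size or SD is printed. If it came from a four-group one-way ANOVA, 80% power with 15 per group implies Cohen's f of about 0.44.

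**2. If any one primary counts as success.** With independent outcomes the familywise error is 1 − 0.95³ = 0.1426, or 14.3%; the upper bound is 3 × 0.05 = 15%. For correlated outcomes, three four-arm ANOVAs at 0.05 were simulated under no effect, with 200,000 runs per setting:

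| Common correlation | 15 per group | 19 per group |
|---|---|---|
| 0 | 14.3% | 14.3% |
| 0.3 | 13.8% | 13.8% |
| 0.5 | 12.8% | 12.8% |
| 0.6 | 12.2% | 12.2% |
| 0.7 | 11.3% | 11.3% |
| 0.8 | 10.3% | 10.3% |
| 0.9 | 8.7% | 8.7% |

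The error stays above 5% in every setting examined. Group size makes no material difference.

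**3. If all three must succeed.** The chance that all three are significant when at least one has no effect is at most 0.05, so alpha is not inflated. The chance of success, however, cannot exceed the 80% set for FMA-UE. As an illustration only, if each outcome had 80% power and they were independent, it would be 0.8³ = 51.2%.

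**4. Comparing remedies.**
- *Fixed order led by FMA-UE.* A false positive requires the first outcome in the order without a true effect to be significant at 0.05, so familywise error is at most 5%. FMA-UE keeps its full alpha and its 80% power with 60 evaluable.
- *Equal split, 0.05 / 3 = 0.0167 each.* Familywise error is 1 − (1 − 0.0167)³ = 4.92% if independent. At f of about 0.44, FMA-UE power falls from 80% to about 65% with 60 evaluable, and is 79% even if all 76 were evaluable. In steps of four patients, 80 evaluable are needed to pass 80%, which is 80 / 0.8 = 100 randomized.

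**The case against.** The strongest objection is that the article never says success on any one primary is enough. The Background separates clinical efficacy from exploring mechanisms, and the abstract ties BDNF to the latter. The Conclusion speaks of an overall evaluation that also draws on the secondary outcomes. A testing order might sit in an analysis plan that is not shown. This stands in part: the error figure must be given as conditional. It does not remove the point. The article prints three unranked primaries, a blanket threshold, and a correction confined to arm comparisons, and the Conclusion treats all three as main indicators of efficacy.

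Three stronger readings are tempting, and the documents do not support them.

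- A reader might infer that sizing on FMA-UE causes the inflation, or that it contradicts the list of three. Sizing does not affect type I error, and sizing on one of several primaries is common. What remains is that power for the other two is not addressed.
- A reader might add FMA-UE at week 6 as a fourth test and quote 1 − 0.95⁴ = 18.5%. That treats two scores from the same patients as independent; with a correlation of 0.8 between them, and the other outcomes independent, it is about 17%. It also passes over the listed repeated measures ANOVA, which handles the visits jointly.
- A reader might take week 2 as the time point behind the sample size. The Sample size section names none.

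Finally, demoting primaries that are already published is more than a change of wording. That is fair, and a fixed order avoids the demotion.

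**Conclusion.** The point holds in conditional form. Followed as written, and if any one primary can carry the efficacy claim, the error rate is 14.3% under independence, about 12–14% for correlations of 0 to 0.6, and about 9–11% for 0.7 to 0.9. The correlations are assumed, and the figures count one omnibus test per outcome. If all three must succeed, error is controlled, but the stated 80% power describes only one component of that requirement. Either way the text needs a decision rule. It is not safe to say simply that the trial's error rate is 12–14%, because the protocol never states the rule on which that depends.

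**What to change.** State in the Data analysis section and in the registry that FMA-UE is tested first, at two-sided 0.05, as the outcome that supports the efficacy claim. Latency and then BDNF follow in that order, each at 0.05 and only if the preceding test is significant. Alternatively, make FMA-UE the sole primary and the other two secondary.

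Name one FMA-UE contrast or time point for the first test. Week 2 is a reasonable choice, because the Study design section has all three outcomes measured then and only clinical behavior repeated at week 6. This is a new choice to be justified in the amendment.

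Fix the rule before any outcome is compared by group codes 1–4. Before unblinding is not early enough, since the Blinding section places unblinding at the end of the analysis. The article gives June 2022 as the start and December 2023 as the expected end, so whether that window is still open has to be confirmed by the sponsor.

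Cost: no added patients; N = 76 stands. Latency and BDNF cannot support a confirmatory claim if FMA-UE is not significant, and the change must be reported as a dated amendment. An equal alpha split is less attractive because of the loss in FMA-UE power shown above.

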**Discussion:**

The findings of this study will help develop optimal stimulation protocols for motor recovery in stroke patients and identify biomarkers that respond to post-stroke motor rehabilitation, for better guidance of clinical treatment.

**Trial registration:**

The study protocol was passed by the Medical Research Ethics Committee of the General Hospital of Ningxia Medical University on January 1, 2022 (no. KYLL-2021–1082). It was registered into the Chinese Clinical Trials Registry on May 22, 2022 (no. ChiCTR2200060201). This study is currently in progress.

**Graphical Abstract:**

[figure not shown]

**Supplementary Information:**

The online version contains supplementary material available at 10.1186/s13063-023-07584-7.

## Background

Stroke is an acute condition resulting from the disruption of blood circulation to the brain, falling under the category of non-communicable disease. According to the Global Burden of Disease (GBD) 2019 report by the World Health Organization [1], stroke is the second leading cause of death worldwide and is associated with a significant rate of disability. If the current trend persists, the projected figures indicate that by 2050, there will be approximately 200 million stroke survivors and 13 million annual stroke-related deaths on a global scale [1]. Up to 85% of stroke patients suffer from upper limb dysfunction [2], which severely impacts their daily life and work, imposing substantial limitations and resulting in a considerable financial burden on society [3].

Current conventional upper-limb rehabilitation methods include central interventions with mirror therapy, motor imagery therapy, peripheral interventions with physical factors, and compulsory movement therapy. However, these conventional methods have some limitations due to the high demands on the patient’s consciousness and subjective motivation with long treatment periods. Thus, it is necessary to develop a fast, efficient, and convenient method to improve upper-limb motor function.

In recent years, repetitive transcranial magnetic stimulation (rTMS) has prevailed in neurorehabilitation as a feasible, safe, and painless neurophysiological technique [4]. Studies have shown that neuroplasticity-induced cortical reorganization is an essential regulatory process in motor function recovery after stroke [5], and substantial research has shown that rTMS can promote brain plasticity [6].

The current rTMS treatment protocols for stroke have diverse forms [7], ranging from initial unilateral hemisphere stimulation with low- or high-frequency rTMS alone, TMS combined with other rehabilitation therapies, to low-frequency rTMS stimulation of the unaffected hemisphere together with high-frequency rTMS of the affected hemisphere. The first two protocols have been studied extensively, while less research has been conducted on the latter.

The clinical trial by Long et al. demonstrated that combined 1 Hz and 10 Hz rTMS was effective for the recovery of upper limb motor function in patients with acute stroke [8]. Chen et al. also found that a combination of low- and high-frequency rTMS could synergistically enhance motor function and cortical excitability in patients with subacute stroke [9]. Nevertheless, few studies have compared the effects of this protocol on upper-limb motor deficits in patients with stroke in the convalescent stage.

In addition, the mechanism of action of rTMS in post-stroke motor function remains unclear. It is commonly believed that low-frequency (1 Hz) rTMS inhibits neuronal excitation in the unaffected hemisphere, whereas high-frequency (> 1 Hz) rTMS induces facilitation in the affected hemisphere [10], thereby impacting intracerebral metabolism and neuroelectrical activity. Biomarkers are usually used as measurable objective indicators to analyze therapeutic efficacy [11].

Brain-derived neurotrophic factor (BDNF), a member of the neurotrophin family, is associated with the regulation of neuronal reorganization and is involved in the pathogenesis of many neurological diseases [12]. BDNF exists in two forms, mature BDNF and BDNF precursor protein (proBDNF), which are functionally opposite [13]; proBDNF can be converted to BDNF by matrix metalloproteinase-9 (MMP-9) [14]. In an animal study, BDNF was revealed to be able to cross the blood–brain barrier (BBB) [15], and its levels in serum correlated well with those in brain tissue [16]. Notably, the concentration of BDNF and pro-BNDF in peripheral blood is considered to be representative of its function in the brain, and serum levels may to some extent reflect brain function [17–19]. Therefore, assessing their levels in individual serum sample will have clinical and scientific implications. In recent years, there are many studies on the relationship between BDNF and stroke, but little attention has been paid to proBDNF and MMP-9.

This trial aims to investigate the clinical efficacy of LF-HF-rTMS on upper extremity motor function in convalescent stroke patients and to explore the mechanisms underlying its therapeutic effects. This study will assess the following: significant changes in clinical behavioral assessments and cortical excitatory parameters in patients with convalescent stroke after 10 interventions with rTMS, compared with that by sham and unilateral hemispheric stimuli. In addition, we will measure the concentrations of neuroplasticity mediators, serum BDNF, pro-BDNF, and MMP-9, and analyze their correlation with behavioral improvement.

## Methods

### Study design

This is a prospective, single-blind, randomized controlled clinical trial with hidden assignment and intent-to-treat analysis. We will recruit 76 patients with upper extremity motor deficits after stroke in convalescence and then randomly and equally assign them to LF-HF-rTMS, low-frequency, high-frequency, and sham stimulation groups. Subjects will be assessed for clinical behavior, neurophysiology, and serologic testing at baseline and after 2 weeks; further follow-up assessment of clinical behavior will be performed after 6 weeks (Fig. 1).

**Fig. 1 Fig1:**
[figure not shown]
The SPIRIT schedule. LF-HF-rTMS, low- and high-frequency rTMS; LF-rTMS, low-frequency rTMS; HF-rTMS, high-frequency rTMS; FMA-UE, Fugl-Meyer assessment-upper extremity; BDNF, brain-derived neurotrophic factors; NIHSS, National Institutes of Health Stroke Scale; MBI, modified Barthel index; MAS, modified Ashworth scale; BS, Brunnstrom staging; CMCT, central motor conduction time; ProBDNF, precursor proteins of mature BDNF; MMP-9, matrix metalloproteinase-9

The protocol was written based on the Standard Protocol Item: Recommendation for Interventional Trials (SPIRIT, S1 File) checklist [20]. This study is in accordance with the latest revised version of the Declaration of Helsinki 2013.

### Recruitment

We will recruit 76 stroke patients with upper-limb movement disorders during recovery from the inpatient unit of the Department of Rehabilitation Medicine at the General Hospital of Ningxia Medical University (Fig. 2). Stroke patients account for the majority of our unit’s patients, and the inpatient period is 2 weeks, which is sufficient to ensure the required number of recruits and interventions. Patients will be recruited through various forms, including WeChat promotion, hospital posters, verbal presentations by physicians, and community outreach. Participating patients enjoy a privileged policy in which all assessments and neurophysiological examinations are free of charge during the treatment period, and registration fees and transportation costs are reimbursed during follow-up visits. Patients who agree to join this study will be recruited, and demographic information and assessment data will be collected and monitored by the attending physician.

**Fig. 2 Fig2:**
[figure not shown]
Recruitment of participants and flow chart. CRT: Conventional rehabilitation treatment

### Inclusion criteria

They will be recruited for the following criteria: (1) those with diagnosis in accordance with the relevant diagnostic criteria for cerebral infarction and cerebral hemorrhage in the “Chinese Guidelines for the Prevention and Treatment of Cerebrovascular Diseases” [21], confirmed by cranial CT or MRI to affect unilateral cerebral hemisphere; (2) disease duration of 30–180 days, and patients with stable vital signs, clear consciousness, and willingness to cooperate; (3) those with the first incidence of stroke; (4) those aged 30–75 years; (5) upper-limb Brunnstrom stages 2–5; and (6) patients and family members are willing to sign the informed consent form.

### Exclusion criteria

These patients will be excluded in case of the following conditions: (1) those with unstable disease, progressive stroke, malignant progressive hypertension, or cerebral hemorrhage secondary to cerebral infarction; (2) those with apparent indications of increased intracranial pressure; (3) those with contraindications to transcranial magnetic stimulation therapy, such as epilepsy, implanted pacemakers or drug pumps, metal objects in the skull or eyes; (4) those with combined cognitive dysfunction; (5) those with combined malignancy; and (6) those with severe lung, heart, liver, and kidney dysfunctions.

### Patient withdrawal criteria

The patient withdrawal criteria are as follows: (1) patients whose decision changes during the disease, rendering them unsuitable for continued treatment, and (2) other personal reasons.

### Randomization

After meeting the inclusion criteria, 76 subjects will be randomly assigned in a 1:1:1:1 ratio to the LF-HF-rTMS, low-frequency, high-frequency, and sham stimulation groups. The grouping will be performed according to a PC-generated random number, which will be concealed in a sealed envelope. The random sequence will be managed and supervised by specific personnel who have no contact with the subjects and are not included in data collection or analysis.

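### The named between-group analyses use no covariate although patients enter 30 to 180 days after stroke; adding days since stroke and baseline FMA-UE would cost almost nothing and could recover some precision.

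*Protocol article*

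**What the plan says.** Inclusion criteria (Protocol article) admits patients with "disease duration of 30–180 days" and "upper-limb Brunnstrom stages 2–5". That is a 150-day window and four of the six Brunnstrom stages listed under Secondary outcomes.

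Randomization states that "76 subjects will be randomly assigned in a 1:1:1:1 ratio" and describes the method as follows: "The grouping will be performed according to a PC-generated random number, which will be concealed in a sealed envelope". It mentions neither strata nor minimisation.

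Data analysis names its models. Between groups it gives "one-way ANOVA for inter-group comparisons, and Bonferroni correction for post hoc comparisons between groups", with Kruskal–Wallis for non-normal data. For the longitudinal comparison it gives a two-factor repeated measures ANOVA whose only factors are time point and group. No covariate appears in any of them.

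Blinding places unblinding after the data analysis. Trial status gives a start in June 2022 and an expected end in December 2023.

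**The concern.** The outcome is change in arm function over 2 to 6 weeks while every arm receives conventional rehabilitation, so background recovery runs alongside any stimulation effect. A patient entered at day 30 is assessed at about days 44 and 72; one entered at day 180, at about days 194 and 222. Their expected further recovery may well differ. Comparing each patient with baseline does not remove this, because time since stroke can affect the rate of change as well as the starting level.

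If time since stroke is prognostic, two things follow from leaving it out. Its contribution stays in the residual variance and widens every interval for the combined arm against its comparators. And if the arms happen to differ in mean time since stroke, the named models have no term that can correct for it. With 19 per arm, moderate imbalance is not rare.

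**Working it through.** **Inputs from the article.** Entry window 30 to 180 days; 76 patients, four arms, 19 per arm; 60 patients (15 per arm) before a 20% dropout allowance; two-sided alpha 0.05; power 0.80.

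**Assumptions, not in the article.** Entry days uniform over the window. Within-arm correlation r between time since stroke and the analysed outcome of 0.2 to 0.5.

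**1. The plan's own figure.** 60 / (1 − 0.20) = 75, rounded up to a multiple of four = 76, or 19 per arm. This reproduces. The 60 cannot be reproduced, because no effect size or SD is stated. Solved backwards, a four-arm one-way ANOVA with N = 60, alpha 0.05 and 80% power implies Cohen f = 0.44. If one arm differs from the other three, f = d√3/4, so d = 0.4415 × 4/√3 = 1.02 SD. This effect is used below.

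**2. Chance imbalance between two given arms.**
- SD of entry day: 150/√12 = 43.3 days.
- Standard error of the difference in means: 43.3 × √(2/19) = 14.0 days, so a 95% range of ±1.96 × 14.05 = ±27.5 days.
- P(difference exceeds 20 days): 20/14.05 = 1.42, two-sided probability 15%.
- P(difference exceeds 0.5 SD, 21.7 days): 12%.

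**3. Effect of such an imbalance on an unadjusted contrast.** The shift is 0.5 × r outcome SD: 0.10 at r = 0.2 and 0.25 at r = 0.5.

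**4. Type I error, 19 per arm (20,000 simulated trials per setting).** Over all randomisations the unadjusted ANOVA rejects in 4.8% to 5.0% for every r. In the tenth of randomisations with the widest spread of arm means it rejects in about 6%, 7%, 9% and 13% at r = 0.2, 0.3, 0.4 and 0.5. With the covariate, the rate in that same tenth is about 4.4%.

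**5. Gain from adjustment.** The share of residual variance removed is r².

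| r | Variance removed | Power, 15 per arm | Power, 19 per arm |
|---|---|---|---|
| 0 | 0% | 80% → 79% | 90% → 89% |
| 0.2 | 4% | 80% → 81% | 90% → 90% |
| 0.3 | 9% | 80% → 83% | 90% → 92% |
| 0.4 | 16% | 80% → 86% | 90% → 94% |
| 0.5 | 25% | 80% → 90% | 90% → 96% |

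Power is for the overall F test with time since stroke as the only covariate. The row r = 0 shows the price if time since stroke turns out not to be prognostic: less than one percentage point. Once baseline FMA-UE is also in the model, r should be read as the correlation that remains after allowing for it.

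**The case against.** The strongest reply is that nothing here is invalid. An unadjusted comparison in a randomised trial already carries chance imbalance in its standard error, and step 4 confirms that overall type I error is held. This stands. A reader might infer that differences in spontaneous recovery bias the trial and could pass for a stimulation effect. The documents do not support that as a systematic fault; it describes only the particular trial that draws a marked imbalance.

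A second reply is that an article condenses a full protocol, and Trial status cites a protocol version that is not shown. Strata or block sizes may be stated there. This also stands, so the silence under Randomization is not evidence that allocation ignores time since stroke. It has less force against Data analysis, where the models are named and their factors listed.

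Third, larger figures are easy to produce but answer a different question. The median gap between the highest and lowest of four arm means is about 20 days, but that takes the worst pair, whichever it is. The aim stated in Background is to compare the combined arm with each comparator, and for one given pair a gap above 20 days arises about 15% of the time. Converting days into FMA-UE points needs a slope that the article does not give. Even an assumed 1 to 3 points per 30 days would imply a difference of 5 to 15 points in natural gain between entry at day 30 and at day 180 (150/30 = 5 intervals), and nothing in the documents supports that.

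Finally, Brunnstrom stage overlaps with baseline FMA-UE, which the repeated measures ANOVA already includes as a time point. The case for adding stage is therefore weaker than the case for days since stroke.

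**Conclusion.** The point holds as a matter of precision and of protection against an unlucky draw, not of validity. The plan fixes between-group models without covariates in a population that spans 150 days of time since stroke, although that value is known for every patient at entry. The benefit of adjustment runs from slight (4% of residual variance, about one percentage point of power at 15 per arm) to useful (25%, about ten points). Where it falls depends on a correlation that the documents do not report. The imbalance figures also rest on uniform entry times; a narrower actual spread would reduce them. The change is worth making because its cost is close to nil even if the correlation is zero.

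**What to change.** Before unblinding, and before any outcome is tabulated by the coded group numbers, prespecify the FMA-UE between-group comparison as an ANCOVA or a mixed model for all randomised patients, with baseline FMA-UE and days since stroke (continuous) as covariates. Keep the Bonferroni correction for the pairwise contrasts. Brunnstrom stage is optional. The unadjusted ANOVA can be reported alongside as a sensitivity analysis.

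The cost is one or two degrees of freedom and a short amendment. Days since stroke is needed to check eligibility and FMA-UE is assessed at baseline, so nothing new is collected. Timing matters: a covariate added only after an imbalance has been seen is a post hoc choice.

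Re-stratifying allocation is not needed. Publication was in September 2023 and the trial was due to end in December 2023, so few patients would be affected. Two binary factors by four arms would give 2 × 2 × 4 = 16 cells, or 76/16 = 4.75 patients per cell even if all 76 were still to be allocated.
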